## 2. DEFINITIONS

**Care team:** The individual or group of medical professionals whose role it is to screen RPM alerts and follow up with the patient, referring to the patient's PCP or other specialists if necessary.

**Home:** Level of residence or health care facility where the patient was residing prior to hospital admission.

**Heterogeneity of Treatment Effects (HTE):** The hypothetical scenario in which the effect of intervention on outcomes depends on baseline covariates.

**Index Hospitalization:** Hospitalization during which patient was enrolled in the clinical trial.

**Intention To Treat (ITT):** All eligible and consented patients who undergo randomization will be included in the ITT cohort for the purposes of analyzing the primary and secondary study outcomes.

**Intervention arms:** RPM-Low + Standard team, RPM-Low + Enhanced team, RPM-High + Standard team, RPM-High + Enhanced team.

**Remote Patient Monitoring (RPM):** An automatic electronic messaging system designed to push questions to patients at fixed intervals. Questions vary depending on the intensity of the RPM program (Low or High), but patient answers can trigger alerts and responses by members of the intervention care team.

**Study day:** The day of discharge to home is study day 0. The next calendar day is study day 1, etc.

**Study hospital:** Defined as the hospital where the patient was randomized and enrolled.

**Study withdrawal:** Defined as permanent withdrawal from study before completion of study activities. If a patient or surrogate requests withdrawal from the study, the clinician should seek explicit permission to continue data collection.

**Prognostic strata:** patient groups with different PDHD distributions.

**Predictive strata:** patient groups in which intervention effects are estimated individually.

### 3. BACKGROUND AND RATIONALE

Readmissions after sepsis or pneumonia exact an enormous toll on the health and quality of life of individuals and pose significant challenges for the health care system. Approximately, one in five Medicare beneficiaries discharged from the hospital are readmitted within 30 days and a third in 90 days, and older adults with multimorbidity are at higher risk. Returning to the hospital after an index admission is shown to worsen patients' quality of life and increase their risk of healthcare-acquired infections, despite the fact that many of these readmissions are avoidable.

Individuals hospitalized for sepsis or pneumonia are particularly at risk for readmission and poor health outcomes. Among 14 million readmissions in the National Readmissions Database, sepsis and pneumonia (~3 million cases annually in US) were leading causes of readmissions. Readmissions following sepsis and pneumonia are more common and associated with higher costs than readmissions due to heart failure, chronic obstructive pulmonary disease (COPD), or myocardial infarction. Survivors of both conditions experience reduced quality of life, increased mortality and morbidity, and cognitive impairment and functional limitations. Despite readmissions, one in three patients do not survive the year following sepsis or pneumonia, and those who do survive often experience persistent health deficits. In a subset of hospitals owned by UPMC, a large integrated delivery and finance system in Pennsylvania, all-cause 30-day readmission rates for individuals with sepsis or pneumonia (23%) exceed the overall average (12%).

Further, readmissions following sepsis or pneumonia are often preventable. Up to half of readmissions after sepsis can be attributed to preventable causes and the preventability of readmission after pneumonia is recognized by the Centers for Medicare and Medicaid Services' (CMS) Hospital Readmission Reduction Program as an indicator of quality of care. Most patients hospitalized with sepsis or pneumonia are >65 years of age and have multimorbidity. Two-thirds of readmissions following sepsis or pneumonia were due to infection (~40%) and cardiovascular (15%) and respiratory disease (10%). In theory, adequately monitoring patients, detecting early signs of deterioration, and triaging them to appropriate care would decrease unnecessary care utilization and increase patient stability. This is the premise of several widespread interventions, such as in-hospital rapid response teams, post-discharge remote patient monitoring (RPM) for heart failure, and primary care-led monitoring, in the community.

However, there are critical gaps in knowledge regarding how comprehensively we should remotely monitor patient symptoms and types of health care teams best suited for responding to alerts to maximize patient time at home. The standard of care for patients with multimorbidity is to provide some level of care coordination or care provision after discharge, as we know it works. There is a large body of evidence demonstrating that post-acute care models as a whole reduce the risk of an individual returning to the hospital after discharge. Among these, more complex interventions that leverage multiple components and multiple care providers have greater effect on maintaining patients at home longer after discharge. Specific successful model components include care coordination/care management activities and patient self-management education.

A key priority for the health care system is understanding how to effectively deploy the post-acute workforce in the community. Structured Telephone Support (STS), or telephonically connecting with patients post-discharge to assess health status, reconcile medications, and provide patient education, is a well-studied and effective strategy. Within UPMC, deployment of STS for several years across a wide population has successfully reduced readmissions. However, STS may be insufficient for patients at higher risk of readmission. For more complex patients, RPM platforms have extended the reach of providers by regularly collecting patient-reported data on vital signs and symptoms, allowing early recognition of worsening disease and deploying interventions promptly. Provider monitoring of symptom exacerbation is important because patients alone are unreliable in reporting worsening symptoms. RPM platforms have received FDA approval, reduced readmissions in multiple observational and randomized controlled studies, and are routinely used in clinical care. While patient acceptability of RPM is high, RPM platforms typically monitor one disease or condition (e.g., heart failure exacerbation in patients hospitalized for heart failure). Given that multimorbidity is associated with hospitalization for serious infection and readmissions are often due to worsening of underlying chronic conditions, utilizing RPM to assess multiple disease states could be more successful in early identification and intervention. However, the optimal post-acute care strategy for patients with multimorbidity is unknown.

Additionally, more information about the spectrum of services delivered within and alongside RPM is critical to effectively meeting patients' needs. There is conflicting evidence about whether models that couple RPM with an alert-triggered provider response (Standard Team) or a more intensive patient engagement model (Enhanced Team) are more effective, the reason for which may be that studies often fail to define specific intervention components. Several studies show that multidisciplinary teams that periodically conduct in-person or virtual home visits and specialize in chronic disease management, care coordination, and patient education about self-management may increase time spent at home. However, this approach is resource intense and may be difficult to scale across large geographic areas. Noting that RPM findings are often confounded by additional in-home care received by both intervention and control groups, one study measured the effect of RPM versus usual outpatient care in a sample of patients not receiving concurrent home-based care and showed decreased emergency department (ED) utilization and hospital length of stay and increased quality of life among the group receiving RPM. The study of RPM without explicit investigation of the model of care into which RPM is built is a critical gap in the comparative effectiveness literature.

## 4. ENROLLMENT CRITERIA

### 4.1. *Population*

This domain enrolls adults hospitalized for sepsis or lower respiratory tract infection, including COVID-19, age 21 and older, medium or high-risk of readmission, and whose primary outpatient physician is willing to participate in RPM.

### 4.2. *Eligibility criteria*

Patients are eligible for this domain if they meet all of the REMAP-level inclusion and none of the REMAP-level exclusion criteria (see Core Protocol Section 6.4). Patients who may be eligible for the REMAP may have conditions that may exclude them from the ACCOMPLISH Domain.

#### 4.2.1. Inclusion criteria for this domain

Patients will be included in this domain if they meet the following criteria:

- UPMC Health Plan member or patient with Medicare Fee-for-Service insurance
- Treated at one of 19 prespecified hospitals for sepsis or lower respiratory tract infection
- Age 21 or older
- Medium or high-risk of readmission

#### 4.2.2. Exclusion criteria from this domain

Patients will be excluded from this domain if they have any of the following:

- Admitted from setting other than home or independent living
- Receiving hospice at the time of admission
- Being discharged on/to hospice or LTAC
- Currently participating in UPMC Advanced Illness Care Program
- Unable to participate in RPM due to lack of technology/internet connection
- Known pregnancy
- Severe, persistent cognitive impairment
- No documented primary care physician (PCP)
- PCP disapproves of the patient potentially being enrolled in remote patient monitoring

## 5. INTERVENTIONS

ACCOMPLISH tests the impact of a set of active arms compared with standardized telephone support (STS):

- **Structured Telephone Support (STS):** Structured telephone support (STS) consists of post-discharge assessment, education, and medication reconciliation delivered telephonically by a case manager, home care as needed, and follow-up appointment with the primary care within seven days post-discharge.

The following types of interventions are used across the active arms:

- **Low-intensity Remote Patient Monitoring (RPM-Low):** Questions are pushed to members three times per week for up to 90-days post-discharge. Questions are limited to those checking vital signs that indicate worsening of infection. Patient answers RPM questions, which trigger high or medium alerts and a response by members of the intervention care team (see below).
- **High-intensity Remote Patient Monitoring (RPM-High):** Questions are pushed to members three times per week for up to 90-days post-discharge. Questions include monitoring vital signs for worsening infection but also ask about factors that would indicate worsening of underlying heart or lung conditions, such as weight gain or shortness of breath. Patient answers to RPM questions, which trigger high or medium alerts and a response by members of the intervention care team (see below).
- **Standard Team:** RPM alerts are screened by a nurse-staffed call center. Nurses determine whether immediate outreach to the member is warranted and facilitate connection to the appropriate care (such as referring the member to their PCP, specialist, or instructing the patient to go to the emergency department).
- **Enhanced Team:** RPM alerts are screened by a nurse-staffed call center and alert a certified registered nurse practitioner (CRNP) to modify care plans. CRNPs, who operate in a palliative care role, have prescribing authority and will also facilitate connection to the appropriate care. In addition to reacting to RPM triggers, CRNPs and other members of an interdisciplinary palliative care team (e.g., social workers, nurses) meet with the patient in-person or virtually at least three times in 90 days, conduct assessments, develop care plans, and complete a physician order for life-sustaining treatment.

Patients are randomized to either STS, or active arm; if randomized to active arm, they are assigned to 1 level of RPM (RPM-Low or RPM-High) and 1 type of care team (standard or enhanced care team), leading to 4 active intervention arms:

- RPM-Low + Standard Team
- RPM-Low + Enhanced Team
- RPM-High + Standard Team
- RPM-High + Enhanced Team.

A graphical representation of the interventions is shown in Figure 1.

Figure 1: Study Design

[figure not shown]

5.1. Timing initiation of interventions

Participants will be enrolled in the

appropriate intervention (as randomized) by their first full week day home from the hospital or skilled nursing facility (SNF). Participants enrolled in a RPM arm will be contacted by a research coordinator by telephone and encouraged to download the RPM application and initiate the program. If enrolled in structured telephone support, they will receive a post-discharge phone call per usual care timing.

5.2. Duration of remote interventions

The duration of standard telephone support will align with usual care, but is expected to be limited to one brief telephone conversation, in most cases. The duration of remote patient monitoring interventions is 90 days.

5.3. Concomitant care

The intent of this trial is to observe participants as they participate in real-world post-discharge health care. Therefore, there are very few concomitant care restrictions. Remote patient monitoring pathways will be paused during hospital readmissions and/or admissions to other inpatient care settings. The RPM program will be stopped if the study team learns that a patient entered hospice or expired. Most of other health care utilization will be observed and analyzed during analysis.

The UPMC Advanced Illness Care (AIC) Program is a 6 month palliative care program offered by UPMC Health Plan to members in need of palliative care. Participants who are known to be currently participating in the Advanced Illness Care program will be excluded from study recruitment. Referrals to this program are made both at hospital discharge and during the course of routine outpatient care. It is rare but possible for a randomized ACCOMPLISH participant to be enrolled into the UPMC Advanced Illness Care (AIC) Program during the three month study intervention period. In the event that a randomized ACCOMPLISH participant is also enrolled in the AIC program, the study team will follow a strict intent to treat study design and continue to collect outcomes data per the established timelines and processes. If the number of randomized participants is greater than 10 at the end of all recruitment and data collection, a sensitivity

analysis will be performed to determine if the AIC participants have significantly different outcomes than the participants enrolled in the study as planned.

## 6. ENDPOINTS

### 6.1. Primary endpoint

The primary efficacy endpoint will be post-discharge home-days (PDHD) recorded over the first 90 days after discharge to the patient's home. Patients will be assigned -1 days if they die before day 90 post-discharge home. Among patients who survive 90 days or more, PDHD is recorded as the total number of days alive and out of acute care hospitals or post-acute care facilities (e.g., inpatient rehabilitation, skilled nursing facilities, long-term care facility). If a patient is readmitted to one of these facilities during the 90 days after returning home, then those days not at home will be subtracted from their PDHD. The following rules will be used to calculate PDHD.

- Home is defined as any location that does not involve insurance claims charged to UPMC Health Plan. This can include the patient's own residence, someone else's residence (family or friend), independent living facility or personal care home. It is not restricted to being the same location at which the patient resided pre-admission, so long as it does not involve UPMC Health Plan claims.
- The index hospitalization and post-acute health care facilities (e.g., long-term acute care facility, ventilator-rehabilitation unit, rehabilitation facility, transitional care units, skilled nursing care, nursing homes) visited following discharge are counted as "hospitals" until the patient is discharged home.
- PDHD can take on integer values from -1 to 90. Any calendar day partially spent in acute care hospitals or post-acute care facilities is counted as a full day for the purposes of calculating PDHD, regardless of whether it was part of the initial admission or any readmission.

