Area Deprivation Index (ADI): The ADI will be a composite score of socioeconomic variables to indicate neighborhood socioeconomic status pulled from administrative data at baseline.

Domain: Care Delivery and Utilization:

Non-urgent outpatient care utilization: The count of non-urgent outpatient visits that occur per participant during the observation period (primary and specialty care visits) will be pulled from claims data at 90 days.

Prior admissions: The number of inpatient admissions in 90 days prior to index admission will be pulled at baseline from claims data.

ICU stay, mechanical ventilation, inpatient dialysis: Whether participant received each type of care during index hospitalization and if so, for how many days will be pulled at baseline from the electronic health record and claims data.

Skilled nursing facility stay: Whether a patient had a post-index hospitalization stay in a SNF for 28 days or fewer before being discharged home.

Index hospital: The location of the index hospitalization, hospital bed size, and hospital teaching status will be pulled from claims data at baseline.

540 A summary of measures is shown below:

| STUDY VARIABLES                                      | DATA SOURCE                                                                | WHEN MEASURED      | HOW MEASURED                                                                                                                         |
|------------------------------------------------------|----------------------------------------------------------------------------|--------------------|--------------------------------------------------------------------------------------------------------------------------------------|
| Primary Outcome                               |                                                                            |                    |                                                                                                                                      |
| Post-discharge home days                             | Claims data, EHR data, Health Information Exchange (HIE) data, Participant | 90 days            | Total number of days alive and out of acute care hospitals, inpatient rehabilitation, or skilled nursing facilities  |

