## 8.11. *Handling of missing data*

### 8.11.1. *Missing PDHD data*

The primary endpoint is ascertained using claims data for the majority of patients, and medical records review for the small subset of patients that either drop UPMC Health Plan coverage during the course of follow up, or are covered by the Medicare Fee-for-Service program. We will assume that no record of death or readmissions counted against the primary endpoint correctly correspond to the absence of these events for the patient, and therefore the primary outcome will be completely observed for all patients.

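### The SAP 6.1 rule that defines home by UPMC Health Plan claims does not fit fee-for-service patients and contradicts the facility-based definition of the primary endpoint

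*Combined protocol and SAP*

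**What the plan says.** SAP 6.1 opens with a definition that does not depend on the payer: among 90-day survivors, "PDHD is recorded as the total number of days alive and out of acute care hospitals or post-acute care facilities". It then takes off days not at home: "If a patient is readmitted to one of these facilities during the 90 days after returning home", those days are subtracted. The rules for the calculation follow, and the first reads: "Home is defined as any location that does not involve insurance claims charged to UPMC Health Plan". The same bullet says that home need not be the pre-admission location, "so long as it does not involve UPMC Health Plan claims". The other two bullets concern facilities and partial days and name no payer.

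Three other places bear on this:

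- SAP Section 2 defines home as "Level of residence or health care facility where the patient was residing prior to hospital admission".
- The protocol's table of measures gives the primary outcome as "Total number of days alive and out of acute care hospitals, inpatient rehabilitation, or skilled nursing facilities", from claims, EHR, health information exchange (HIE) and participant data.
- SAP 8.11.1 uses claims for most patients and "medical records review for the small subset of patients" who lose Plan coverage or have fee-for-service Medicare. Where no death or readmission is on record, it assumes that none occurred, and it treats PDHD as fully observed.

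Eligibility under SAP 4.2.1 is "UPMC Health Plan member or patient with Medicare Fee-for-Service insurance". SAP 8.9.7 dates the fee-for-service extension to August 10, 2022.

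**The concern.** The claims bullet is one of the instructions for deriving the primary endpoint. For a fee-for-service patient, a member whose coverage has lapsed, or a stay paid for by someone else, a hospital or nursing-facility stay produces no Plan claim, so under the bullet the place counts as home. Under the opening definition of the same section it does not. A fee-for-service patient readmitted for ten calendar days scores 90 under one reading and 80 under the other, so two programmers could build different primary datasets from the same records.

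The bullet can also work the other way. Its closing condition would let a residence where a service is billed to the Plan count as not home.

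PDHD drives adaptive allocation (8.7), the futility rule (8.8) and the success criterion (8.9.1), so an ambiguous score reaches every decision in the trial. Facility days scored as home days dilute a real effect and cost power.

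**Working it through.** **Which rule removes a facility day?**

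| Place | Basis for home | Payer condition |
|---|---|---|
| SAP 6.1, opening text | outside acute and post-acute facilities | none |
| SAP 6.1, first bullet | no Plan claim | Plan only |
| SAP 6.1, second and third bullets | facility stay, whole or part day | none |
| SAP Section 2 | pre-admission residence or facility | none |
| Protocol, table of measures | outside three facility types | none |
| SAP 8.11.1 | records review outside the Plan; no record means no event | source differs by coverage |

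The first bullet conflicts with the opening text and with the protocol table. Section 2 conflicts with the bullet's own statement that home is not tied to the earlier location. SAP 8.11.1 changes the data source but not the rule.

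**Reproducing the plan's figures.** The Table 2 distribution (death 0.133, 90 days 0.454; it sums to 0.999 and was rescaled to 1) was shifted by logit(c′) = logit(c) − ln(OR), where c is a cumulative probability. For the baseline stratum this gives death and 90-day probabilities of 0.133 and 0.454 at OR 1.00, and 0.093 and 0.555 at OR 1.50. Table 4 states 0.13 and 0.45, and 0.09 and 0.55.

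**Literal reading, every outside stay missed.** All fee-for-service survivors score 90, so P(90) = 1 − 0.133 = 0.867 instead of 0.454. The wrongly scored share of survivors is 1 − 0.454/0.867 = 0.476.

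**Effect on the estimate.** Let f be the fee-for-service share. In both arms, a share f of the 0–89 probability moves to 90, and one proportional-odds ratio is fitted to the expected counts. The information factor is I = 1 − Σp̄³, with p̄ the two-arm average.

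**Effect on power.**

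- The 0.991 threshold (8.9.1) corresponds to z = 2.366. Arm 4 power in scenario 3 is 0.851 at 1,500 (Table 5.2), which corresponds to z = 1.041. The drift is therefore 2.366 + 1.041 = 3.406 (from unrounded values).
- Complete patients: 1,281 × (1 − 0.025) = 1,249, using the 2.5% loss in the November 2023 power section. The drift becomes 3.406 × √(1249/1500) = 3.108.
- Power with no misclassification: Φ(3.108 − 2.366) = 0.77. The plan's own table gives 0.765 at 1,200 and 0.782 at 1,250 and says that its approximations may be slightly aggressive.
- With misclassification: drift = 3.108 × ln(fitted OR)/ln(1.5) × √(I/0.859).

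| f (assumed) | Fitted OR | I | Drift | Power |
|---|---|---|---|---|
| 0 | 1.50 | 0.859 | 3.11 | 77% |
| 10% | 1.48 | 0.830 | 2.94 | 72% |
| 20% | 1.46 | 0.797 | 2.78 | 66% |
| 30% | 1.44 | 0.757 | 2.62 | 60% |

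The rows can also be read for partial misses. A 30% share in which one third of the affected patients have their stays wholly missed equals the 10% row.

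**Cross-check.** A second calculation mixed the plan's strata (11% severe, 37% SNF) and used the scenario 3 mean arm sizes at 1,500 (STS 450, arm 4 607). It gives power of 0.847 with no misclassification (stated 0.851), then 0.81, 0.76 and 0.72 at the same three shares. The 0.847 uses the unadjusted fitted OR of 1.47; with OR 1.5 the formula gives 0.88 to 0.89, so it checks direction and order of size only.

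**The case against.** A reader might infer that the plan scores every surviving fee-for-service patient as 90 home days. The documents do not support that. The opening text of 6.1 removes facility days whoever pays, as do its second and third bullets. SAP 8.11.1 sets up records review for exactly these patients, which would serve no purpose for facility days if the claims bullet decided the score. Nothing shows that PDHD has been derived by the bullet alone.

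A reader might also infer that billed home care takes home days away. That is not established either. SAP 6.1 names the patient's own residence as home and subtracts facility days, and no section says that home care or team visits produce Plan claims. It is an ambiguity.

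More stands on that side:

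- The protocol table is largely a short form of the opening text of 6.1, so the two agree in principle. Their facility lists still differ, because 6.1 adds long-term care and nursing homes.
- Patients admitted from outside home or independent living are excluded (the protocol also allows personal care homes), so the facility wording in Section 2 has little practical reach.
- SAP 8.9.7 plans models with payer terms and payer-specific intercepts, and 8.9.8 restricts to continuously covered members. The protocol sends home-day distributions by payer to the DSMB.
- Within a wholly misclassified fee-for-service group the odds ratio stays at 1.5. The drop in the estimate comes from common intercepts across payers, which the payer-specific-intercept model would remove, leaving only the loss of information.

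These points limit the size of the problem, but they do not settle which rule governs. The sensitivity models cannot tell a true payer difference from a difference in measurement, and 8.9.8 itself allows that ascertainment may be better among continuously covered members.

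**Conclusion.** The rule is wrong as written. It defines home by one payer's claims in a trial with two payer groups, and it contradicts the facility-based definition beside it, the protocol table and SAP Section 2. SAP 8.11.1 reduces the exposure but names only records review and takes no record as no event, so the practical risk is outside stays that the review misses. Recruitment includes non-UPMC hospitals, so such stays are foreseeable.

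The calculated loss (OR 1.5 estimated as 1.48, 1.46 or 1.44; power from about 77% to 72, 66 or 60%) is an upper bound for missed stays at each assumed share. It assumes that every stay is missed, all deaths are found, misclassification is equal across arms and all patients follow the baseline-stratum distribution. The share is not given, and 8.11.1 describes these patients together with those who lose coverage as a small group, so the real loss may be well below these figures.

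Unequal ascertainment by arm is possible, because RPM staff review non-responders' charts for readmission and death while STS is usually one call. The documents do not say whether those reviews feed the endpoint, so no bias between arms is shown.

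**What to change.** Replace the claims-based bullet with one payer-neutral rule, worded identically in SAP Section 2, SAP 6.1 and the protocol's table of measures. A day is not a home day if any part of it is spent as an inpatient or resident of a listed facility type, whoever pays. Outpatient and home-care claims do not remove a home day. Use a single facility list; the one in 6.1 is the fuller of the two.

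In SAP 8.11.1, state that for fee-for-service and lapsed-coverage patients, facility days and deaths come from EHR and HIE data, and facility days also from participant report. The protocol table already lists these sources for the primary outcome.

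The cost is wording changes in both documents and some added derivation work for these patients, from sources already collected. No new data collection and no change to the analysis model are needed.
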